## Methods/design

### Study design

The impact and benefit of the PEP will be evaluated by comparing the educational approach and the “conventional” management of pain. The Step 5 of the EFFADOL project is a multicentre, stepped-wedge, cluster randomised controlled trial. This particular randomised design known as the step-wedge procedure [17–19] minimize the risk of contamination between the two groups (conventional vs TPE approach) and thereby the risk of bias. Indeed, when the purpose is to compare two practices (in this case, TPE and conventional care) in which the attitudes of the caregivers are changed, it is critical to set up at the same time, and with the same health staff the two assessed different modes of care. The stepped-wedge design particularly suits in such setting since it makes it possible to stagger the training of the caregivers hospital by hospital and consequently that of the educational intervention per participating centre. The randomisation is performed at the cluster level, instead of the patient level.

Thus, 6 clusters will be formed in which TPE dispensing will be strictly identical. The first cluster includes 11 participating centres from Basse-Normandie where enrolled patients will all receive the educational approach as healthcare (physician/nurse) staff at the regional level have been already trained in TPE (Step 1 of the EFFADOL project). Then, five other clusters that correspond to five participating centres outside the region at the national level will be gradually included in a stepped-wedge design (Fig. 1). Finally, the conventional approach (before training) will be compared to the educational approach (after being trained).

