### Statistical analysis

#### Sample size calculation

The calculation of the number of subjects needed for statistical significance is based on the main judgement criterion and on the first secondary endpoint.

To meet the first primary objective (Step 5 of the study) building on a stepped-wedge design, the calculation of needed number of patients is based on a ≥ 2-point decrease of the mean score of the BPI subscale 9 at 8 weeks after inclusion, in the experimental PEP group compared to the control group (corresponding to a clinically significant improvement). The calculation takes into account that randomisation is done by clusters (patients belonging to a same cluster are not independent). Based on bilateral test and common-factor variances (2.5-point standard deviation in both groups (intraclass correlation coefficient = 0.05; 3 clusters per randomisation arm; alpha = 5%; power = 80%) it is estimated that 45 patients per arm equitably distributed between the 6 clusters, for a total of 90 assessable patients (Fig. 3).

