#### Data analysis

At every stage of the analysis, exploratory data will provide, for quantitative variables, mean, its standard deviation, median, quartiles, and missing data; for qualitative variables, frequencies and 95% confidence interval. Statistical tests and confidence intervals will be calculated with an overall error significance level of 5%. For the main objective (Step 5), statistical analysis will be done on the per-protocol population: it will concern assessable patients who have completed the whole program (3 sessions after the educational diagnosis).

Pain interference with daily life scores at 8 weeks post inclusion will be first compared between experimental PEP group and control group, in consideration of the correlation of data (generalized linear mixed model).

For the first secondary objective (Step 4), patients’ adherence to the PEP at the regional scale will be assessed using one-sided test comparing a proportion to a reference value.

For all the steps, a global analysis will be performed, taking into account the different periods of the study, clusters, and the care provided for each period, using a generalized linear mixed model for scales scores and for qualitative results obtained from questionnaires. This analysis will be adjusted to the patients’ demographic and clinical characteristics.

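### Two analyses are given for the Step 5 main outcome, and the protocol does not say that the period-adjusted one decides it

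*Protocol article*

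**What the plan says.** All references are to the protocol article.

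- **Data analysis, main objective.** After fixing the population for Step 5, the text says: "Pain interference with daily life scores at 8 weeks post inclusion will be first compared between experimental PEP group and control group". The model is a generalised linear mixed model, and the only feature mentioned is that it allows for correlation. Study period is not mentioned.
- **Data analysis, all steps.** After a sentence on Step 4, the text adds that "a global analysis will be performed, taking into account the different periods of the study, clusters, and the care provided for each period". This is also a generalised linear mixed model. It covers scale scores and qualitative questionnaire results, and is adjusted for patients' demographic and clinical characteristics.
- **Study design.** Basse-Normandie contributes only patients under the educational approach. Five national centres join in a stepped-wedge order, and the contrast is between care before and care after staff training.
- **Sample size calculation.** Step 5 is sized for a "≥ 2-point decrease of the mean score of the BPI subscale 9 at 8 weeks after inclusion", with a "2.5-point standard deviation in both groups" and "intraclass correlation coefficient = 0.05; 3 clusters per randomisation arm; alpha = 5%; power = 80" per cent. No term for study period appears.

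**The concern.** In each national centre, control patients are recruited before the staff are trained and PEP patients afterwards. Exposure is therefore tied to later calendar time by design. A random cluster effect deals with similarity among patients of one centre. It does not remove a change over time that affects all centres, such as a shift in analgesic practice, case mix or referral. A model with condition and cluster but no period attributes part of any such change to the programme.

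The article attaches the 8-week interference score and the main objective to the comparison that does not mention period, and puts it first. The model that does account for period comes later, under a general heading for all steps, with no statement that it decides Step 5. The two models can give different estimates and different standard errors for the same outcome, and only one of them is protected against a time trend. Without a stated order of precedence, the headline result could rest on the unprotected one.

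**Working it through.** **1. The plan's own figure.** Inputs: difference 2, SD 2.5, two-sided alpha 5%, power 80%, ICC 0.05, 3 clusters per arm.

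- Individually randomised: n = 2 × (1.960 + 0.842)² × 2.5² / 2² = 24.5, i.e. 25 per arm (26 with the usual t correction).
- Design effect with 15 per cluster: 1 + 14 × 0.05 = 1.70. Then 25 × 1.70 = 42.5, i.e. 43 per arm.
- From 26 with three clusters fixed: m = 26 × 0.95 / (3 − 26 × 0.05) = 24.7 / 1.7 = 14.5, i.e. 15 per cluster and 45 per arm.

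This matches "45 patients per arm equitably distributed between the 6 clusters, for a total of 90 assessable patients". It is a parallel-cluster calculation. It neither includes a period effect nor shows whether the analysis will.

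**2. Assumptions for the check.** Figs. 1 and 3 are not shown, so the layout is assumed. The patient counts follow from the text: 230 evaluable − 80 in Basse-Normandie − 75 controls (5 × 15) = 75 PEP patients, taken as 15 in each national centre. With the 15 Basse-Normandie patients assigned to Step 5, that makes 165 patients. Six periods, numbered 0 to 5, are assumed; national centre k (1 to 5) switches at period k. The total variance 2.5² = 6.25 splits into 0.3125 between clusters and 5.9375 within.

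Three layouts:
- A: recruitment spread evenly over all available periods.
- B: each national centre recruits only in the period before and the period after its switch; Basse-Normandie recruits in the first period.
- C: as B, with Basse-Normandie spread over all periods.

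**3. The period-free estimate.** It combines two sources.

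- Within the five centres: variance 5.9375 × (1/15 + 1/15) / 5 = 0.158.
- Between Basse-Normandie (all PEP) and the average of the national centres (half PEP): the difference estimates half the effect and must be doubled. Variance 4 × [0.3125 + 5.9375/15 + (0.3125 + 5.9375/30)/5] = 3.24.

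Precisions are 6.316 and 0.308, so the within-centre weight is 6.316 / 6.624 = 0.953 and the SE is √(1/6.624) = 0.389.

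Bias per unit of linear drift per period:

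- A: within each centre the mean PEP period exceeds the mean control period by (k+5)/2 − (k−1)/2 = 3. The between part is 2 × (2.5 − 2.5) = 0. Bias = 0.953 × 3 = 2.86.
- B: within part 1, between part 2 × (0 − 2.5) = −5. Bias = 0.953 − 0.047 × 5 = 0.72.
- C: within part 1, between part 0. Bias = 0.95.

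**4. Consequences.** Type I error is P(|Z + bias/SE| > 1.96). The period-adjusted SE comes from generalised least squares with a fixed effect for each period; its bias is zero when the time trend is common to all clusters. Power is Φ(2/SE − 1.96).

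| Layout | Bias ÷ drift | Bias, drift 0.1 / 0.2 | Type I error, drift 0.1 / 0.2 | SE without / with period | Power for 2 points, with period |
|---|---|---|---|---|---|
| A | 2.86 | 0.29 / 0.57 | 11% / 31% | 0.389 / 0.616 | 90% |
| B | 0.72 | 0.07 / 0.14 | 5% / 7% | 0.389 / 0.424 | >99% |
| C | 0.95 | 0.10 / 0.19 | 6% / 8% | 0.389 / 0.445 | >99% |

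Simulated trials under layout A with drift 0.2 and no true effect, fitted by REML with a normal reference (two sets of 3,000), agree. The period-free model averages 0.57 to 0.58 and rejects in 31% to 33%. The period-adjusted model averages about zero and rejects in about 6% to 7%, a little above 5% because six clusters are few for a normal reference.

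**The case against.** The strongest reply is that period adjustment is already planned. The global model applies to all steps, hence to Step 5, and to scale scores, hence to BPI interference. It has the terms that a stepped-wedge analysis needs. The comparison made first may be only the opening step of a sequence that ends there, and a phrase about correlation does not exclude further fixed effects. A journal article also condenses a fuller protocol, and a full model specification is normally left to that document or the SAP. The size of the bias rests on a layout and a drift that the documents do not give.

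Much of this stands. A reader might infer that the trial ignores calendar time altogether; the article does not support that. A reader might also take 31% as the type I error to expect; that figure needs both the least favourable layout tried and an assumed drift. Nor can one say that the period-free result will look better for the programme. A trend towards less interference would flatter it, and a trend towards more would mask a benefit.

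What does not fall away is precedence. The article itself describes two analyses of its main outcome, links the main objective explicitly to the one that does not mention period, and never says that the other decides. That is a primary analysis fixed ambiguously, not a detail left for later.

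**Conclusion.** The point holds as one of precedence. A period-adjusted model is planned but not made the deciding analysis of Step 5, and the text reads more naturally as giving that role to a comparison without period. If that comparison decides and has no period term, it is confounded with calendar time. The bias is about 0.7 to 2.9 times the drift per period. At an assumed 0.2 points per period that is 0.14 to 0.57 points against a target difference of 2, with type I error of about 7% to 31%; at 0.1 per period, about 5% to 11%. The direction is unknown.

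These figures assume 165 patients, six periods, the three layouts above, a linear drift common to all clusters, and the protocol's SD and ICC. The structural conclusion needs only the fact that control patients precede PEP patients in the national centres.

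**What to change.** State in the Data analysis section that the primary Step 5 analysis of the 8-week BPI interference score is the mixed model with condition, study period and cluster, adjusted for patient characteristics including baseline BPI interference. Label the comparison without period as descriptive. A cluster-by-period effect and small-sample degrees of freedom are refinements that can be settled in the SAP; this point does not depend on them.

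The cost is a change of wording and a wider confidence interval: SE about 0.42 to 0.62 instead of 0.39 under the assumed layouts. Power for a 2-point effect remains about 90% or more on the assumed 165 patients. That uses a normal approximation, which is optimistic with six clusters.

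### With five crossing centres, the primary mixed-model test needs a named small-sample method, and the planned power makes no allowance for few clusters

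*Protocol article*

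**What the plan says.** Under Data analysis, the protocol article plans to compare the pain interference scores at 8 weeks between the programme and control groups "in consideration of the correlation of data (generalized linear mixed model"). A global mixed model with period, cluster and type of care follows. The same section sets the level: "Statistical tests and confidence intervals will be calculated with an overall error significance level of 5" per cent. It does not name the estimator, the degrees of freedom or a small-sample correction.

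Under Study design, six clusters are counted. The first, Basse-Normandie, gives the programme to all its patients. Crossing from control to programme is left to "five other clusters that correspond to five participating centres outside the region at the national level".

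Under Sample size calculation, the target is a "2-point decrease of the mean score of the BPI subscale 9 at 8 weeks after inclusion". The other inputs are given as "Based on bilateral test and common-factor variances", "2.5-point standard deviation in both groups" and "intraclass correlation coefficient = 0.05; 3 clusters per randomisation arm; alpha = 5%; power = 80" per cent. The result is 45 assessable patients per arm, 90 in all, spread evenly over the six clusters.

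**The concern.** Normal-reference tests and intervals from a mixed model are justified for many clusters. Here the between-cluster variance is estimated from five or six units. In a good share of trials the estimate is zero, and the model then treats patients as independent. The standard error is on average too small, the interval too narrow, and the test rejects somewhat more often than 5%.

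The sample size raises the same issue from the planning side. Three clusters per arm leave 4 degrees of freedom for a comparison of cluster means, yet the stated 45 per arm is what a normal-quantile formula gives. If the analysis later uses a small-sample method, as it should, the 80% power figure no longer matches it. If the method stays open until the data are in, corrected and uncorrected results could fall on opposite sides of 5%.

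**Working it through.** **Inputs.** From Sample size calculation: difference 2 points, SD 2.5, intraclass correlation 0.05, 3 clusters per arm, two-sided 5%, 80% power, 45 per arm (15 per cluster). The same section asks for 15 control patients in each of five regions, 80 patients in Basse-Normandie (15 of them in the primary comparison) and 230 evaluable in total. Since 230 − 80 − 75 = 75, each crossing centre also contributes 15 programme patients. The stepped wedge therefore has 150 patients in the crossing centres, or 165 with the 15 from Basse-Normandie.

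**1. Reproducing the plan's figure.**
- Without clustering: n per arm = 2 × (1.96 + 0.8416)² × 2.5² / 2² = 24.5.
- Design effect at 15 per cluster: 1 + 14 × 0.05 = 1.70.
- 24.5 × 1.70 = 41.7 per arm, which becomes 45 when 3 clusters of 15 are used. The figure is reproduced with normal quantiles.

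**2. Power at 45 per arm on that 3-versus-3 basis.**
- SE = √(2 × 6.25 × 1.70 / 45) = 0.687; 2 / 0.687 = 2.91.
- Normal reference: Φ(2.91 − 1.96) = 82.9%.
- t reference, 3 + 3 − 2 = 4 df, critical value 2.776, non-centrality 2.91: 59.5%.
- On 4 df, 80% power in this layout would take 54 per cluster, or 162 per arm.

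**3. Error rate of an uncorrected test in the stepped wedge.** Trials with no true effect were simulated (10,000 per scenario, Monte Carlo error about 0.2 points). The model was a linear mixed model with a random cluster intercept, fitted by REML, with a Wald test at 1.96. Assumed, because the design figures are not visible: six periods, one centre crossing per step, patients spread evenly over periods. Results at intraclass correlation 0.05:

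| Model and situation | 165 patients | 150 patients | 90 patients |
|---|---|---|---|
| No period term, no time trend | 5.4% | 5.0% | 6.5% |
| Period in the model | 6.5% | 6.5% | 7.2% |
| Period in the model, half the correlation period-specific | 7.0% | 6.6% | 7.0% |
| Period in the model, Kenward-Roger | 5.0% | 4.6% | 3.5% |
| As above, half the correlation period-specific | 5.1% | 4.4% | 3.1% |

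With period in the model and a constant correlation, the uncorrected model's standard error is about 5 to 6% too small. A repeat simulation of the uncorrected REML test gave 5.2 to 5.9% without period, 6.2 to 6.4% with period, and 6.7 to 8.0% with half the correlation period-specific.

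**4. What moves the figure.** Maximum likelihood instead of REML gives 7.6 to 8.9% with period in the model. An effect that varies between centres with SD 0.5 points gives 7.4 to 8.0%, still with REML. The highest values, 9.3% with period and 10.4% without, came from placing 15 patients just before and 15 just after each switch, with half the correlation period-specific.

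**5. Permutation test.** Permuting the crossover order of the five centres (5! = 120 orders, smallest p = 1/120) gave 4.3 to 4.7% under no effect. In a simulated stepped wedge of five centres with 30 patients each, power for a 2-point effect was about 77% by permutation, against an apparent 89% by the uncorrected Wald test.

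**The case against.** The strongest reply is that the article never says an uncorrected normal-reference test will be used. It names a model, and the reference distribution is the kind of detail that a condensed article leaves to the full protocol or analysis plan. A sample size formula with normal quantiles does not fix the later test either. This stands: the error rate can be stated only conditionally, and the missing detail is not in itself an error.

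Three stronger readings are tempting and are not supported:
- A reader might infer that the 5% level is certainly not delivered. At the plan's own inputs, the comparison without period runs at 5.0 to 5.4% in the 150- and 165-patient layouts. The crossing design takes most of its information from within centres, so the excess is modest. The figures above 8% need an added assumption (maximum likelihood, or a particular correlation or timing of patients) that the article does not state.
- A reader might infer that the error favours the programme. The test is two-sided, and under no effect false rejections fall about equally on both sides. A two-sided 6.5% is roughly 3.25% false claims of benefit, against 2.5% nominal.
- A reader might infer that the trial has only 59% power. That figure describes 3 versus 3 parallel clusters. For a stepped wedge of 150 patients the permutation test had about 77%.

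What the reply does not remove is the power statement. The article fixes 3 clusters per arm and 80% power together, and the pair holds only if the cluster count is ignored.

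**Conclusion.** The point holds in a limited form. If the planned mixed-model test is read against a normal reference without small-sample correction, its two-sided error is about 5 to 8% instead of 5%, and its intervals are slightly narrow. This rests on the plan's SD and intraclass correlation, REML estimation, and the assumed six periods with one centre crossing at each step. The article leaves the reference distribution open, so this is a risk to close and not a demonstrated fault of the analysis.

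The sizing statement is the firmer part. On its own stated basis, 45 per arm gives about 83% power by normal quantiles and about 59% on 4 degrees of freedom, so it makes no allowance for few clusters. The power of the design that will be run is a separate figure, and the article does not give it.

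**What to change.** State in the protocol or analysis plan that the primary Step 5 p-value and interval come from one of two sources:
- the period-adjusted linear mixed model with Kenward-Roger standard errors and degrees of freedom; or
- a permutation test over the centre orders that the randomisation allows. There are 120 if one centre crosses per step without restriction. Basse-Normandie is not permuted, because its place was not randomised.

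The period adjustment belongs to the fix. In the 150-patient layout with half the correlation period-specific, Kenward-Roger applied without period only moved the error from 7.5% to 7.2%. Restate the power for the stepped-wedge design on the chosen basis. A centre-by-period random effect can serve as a sensitivity analysis.

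The cost is one or two sentences and little computing. Intervals become somewhat wider and the power figure less favourable. Neither method is perfect. Kenward-Roger was conservative with 90 patients (3.1 to 3.5%), and it stayed at 5.7 to 6.2% in the 150- and 165-patient layouts when the effect varied between centres with SD 0.5. The permutation test cannot give a p-value below 1/120.

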#### Internal validity of the methodology

The choice of the BPI subscale 9 as main endpoint is based on different scientific arguments.

BPI-sf is one of the most widely used pain assessment instrument. Besides pain severity, this questionnaire evaluates the impact on interference. The IMMPACT (Initiative on Methods, Measurement, and Pain Assessment in Clinical Trials) panel recommended that this criterion should be included in all chronic-pain clinical trials [33, 34]. This consensus panel specifically identified the interference items of BPI as one of the scales recommended for the assessment of pain-related functional impairment [35] with a high reliability (*Cronbach alpha reliability ranges from 0.77 to 0.91*). It has been translated and validated in French [22] and the subscale 9 has been recommended by the HAS to assess pain interference with daily life [23].

## Discussion

Nearly one of two patients with cancer pain is undertreated [36]. Patients’ attitudinal barriers in cancer pain remain frequent and are associated with less pain control [37]. Active patient involvement and self-management education appears to be a relevant approach in this regard [38].

In this context, we developed a 5-step project responding to some objectives of the regional health policy and of to third French cancer plan [39]. The construction of a regional PEP, after healthcare staff training to TPE, was based on prior identification of patients’ educative needs regarding cancer pain. PEP implementation will be evaluated through two research steps, first on a regional scale and then on a national one, object of the present study.

In clinical trials, RCT are considered the gold standard of evaluation and as such are mainly used to validate the impact of PEP [10, 38]. The recent systematic review of Oldenmenger et al. [10] reported an improvement in pain intensity in 31% of the PEP studies. The authors incriminate the possible contamination of the control group which could lead to underestimate the actual effect of PEP. In this project, a particular design known as the stepped-wedge procedure was chosen since it allows in particular to provide some control of confounding factors through cluster randomisation [40].

This paper therefore presents the design of a stepped-wedge cluster randomised controlled trial to investigate the effectiveness of TPE in improving cancer pain self-management. The impact and benefit of PEP will be evaluated by comparing the educational approach and the “conventional” management of pain.

The most commonly used criteria to evaluate pain improvement in PEP is pain intensity [9]. Nevertheless, assessment of pain interference with daily life was retained as main endpoint in this study as it appears to less fluctuant and more realistic. Pain interference constitutes in this regard a relevant measure of enhancement in QoL, the latter being the ultimate goal of TPE.

We also took a special interest in educational specifically addressed parameters. Besides patients’ knowledge and attitudes, patients’ communication skills and active participation in their pain management will be assessed.

Satisfaction with treatment might act as a contributor to other outcomes and encourages patient involvement in pain management. Patient satisfaction with cancer pain care strongly correlates with retrospective ratings of overall improvement [29]. Patient-reported improvement scale will be retrospectively measured following the PEP in order to assess the patient’s feeling of changes in his health as well as a clinically significant change.

In addition, evaluation of participants’ and educators’ satisfaction with the program will be used to further optimize the latter by adjusting the followed procedures in necessary.

In conclusion, the originality and strength of this project are based on collaborative work between healthcare professionals and a research approach building on robust methodologies that seek to demonstrate the effectiveness of TPE in improving the patients’ skill in cancer pain management. Dissemination of this educational approach (at regional and then national level) will likely be accompanied by a long term change in practices that should provide mutual benefit to patients and caregiver-educators.

Besides the benefit of PEP for individuals, cancer pain is a national challenge and better managing it is a major public health issue. In this regard, TPE, by giving an impetus to changing patterns of behaviors and attitudes, constitutes an asset to allow better assessment, treatment, and understanding of the problem.

